#### Methods for Additional Analyses (eg, Subgroup Analyses)

Exploratory subgroup analyses will be conducted to understand the extent to which demographic characteristics and country location moderate the effects of the intervention on stigmatization and secondary outcomes.

We will also use regression models to describe the potential effects of demographic factors on participant engagement. To quantify this engagement, we will use Qualtrics to offer participants voluntary posttrial access to the SAS video intervention. We will record a timestamp when the participant reaches the end of the second time point, the moment when a participant chooses to play the video and the moment when they end the study. Participants who skip the video or watch it for less than 3 seconds will be considered as not having engaged with the video. For the participants who watch the video, we will record the length of time spent watching it.

#### Methods in Analysis to Handle Protocol Nonadherence and Any Statistical Methods to Handle Missing Data

Participants in the study will have 45 minutes to watch the short, animated storytelling video and answer their surveys. All items of each survey are designed such that individual items must be answered before moving forward. This will guarantee that there will be no missing values in the datasets of participants included in the analyses. All participants who have completed the first part of the study (T1) will be included in the second part (T2). If a participant, who submitted a completed survey at T1, fails to complete a survey at T2, their data will be included only in the immediate effect analysis. Participants who do not watch the videos or answer the questionnaire items at either time point will be excluded from the analysis.

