#### Sample Size

We calculated the sample size needed for comparing mean scores between the 3 arms, as detailed in the trial design. This was performed independently for the primary and secondary outcomes based on the score of each survey, upon which we selected the most conservative sample size for our study.

We assume that a significant, sustainable change in addiction stigma from watching the SAS video could be achieved by multiple exposures to the video or similar SAS interventions in a series of “micro-doses.” As our study measures the effect of a single exposure to a single SAS video, we aim to measure a small change in our mean outcome scores, presuming that these small changes could yield larger ones following repeated exposures (microdoses). Thus, we have powered this trial to detect a small effect size for comparing the mean scores between trial arms, that is, *d*=0.1, smaller than the generally recommended threshold for detecting a small effect size [31].

We used the sample size formula for a 1-tailed comparison of the mean scores with equal variance, a Type I error of 0.01 to account for multiple comparisons, and a power of 80% to detect changes in the mean scores. This resulted in a sample size of 1128 individuals per arm. Accounting for a potential attrition rate of 20% (personal communication with ProA), this yields 1410 individuals per arm. For this study, we will recruit 1500 participants per arm in each of the 3 countries. This gives us a total sample size of 13,500 participants, which allows us to detect the potential effects of the intervention with a power higher than 80%.

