#### Criteria for Discontinuing or Modifying Allocated Interventions

Participants can withdraw their consent to participate at any time, before or during the study. Incomplete survey data will not be used in the primary analysis, except at a meta-level to report the aggregate number of incomplete surveys.

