##### Primary Outcomes

For each participant, stigma scores will be calculated individually. The mean score for each study arm at T1 and T2 will be calculated and compared between the intervention arms and the control arm at T1, and between the intervention arms and the control arm at T2, using repeated measure ANOVAs. This will be done at the study level and the country level to identify differential effectiveness across geographic conditions. We will also use multilevel regression analyses to control for demographic factors and other potential variables as needed. All analyses will be conducted in R (R Core Team, 2021).

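### The 2-week comparison is limited to T2 completers although 12–20% are expected to miss T2, and the repeated-measures ANOVA, if run as one T1-by-T2 model, would drop those participants from T1 as well

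*Protocol article*

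**What the plan says.** The missing-data section (Methods in Analysis to Handle Protocol Nonadherence and Any Statistical Methods to Handle Missing Data) makes three statements that bear on this point:

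- Every item must be answered before moving on, and "This will guarantee that there will be no missing values in the datasets of participants included in the analyses".
- For a participant with T1 but no T2, "their data will be included only in the immediate effect analysis".
- A closing exclusion covers non-viewers, and it also says that people who fail to "answer the questionnaire items at either time point will be excluded from the analysis".

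The section on discontinuing or modifying interventions adds: "Incomplete survey data will not be used in the primary analysis".

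Under Primary Outcomes in the statistical methods, "The mean score for each study arm at T1 and T2 will be calculated and compared", with the intervention arms set against control at T1 and then "between the intervention arms and the control arm at T2, using repeated measure ANOVAs". Multilevel regression follows as an addition, to control for demographic and other variables as needed. Baseline stigma is collected (Randomization, Consent, and Study Design) but is not named in the primary comparison.

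The Sample Size section allows for 20% attrition, and the pilot reported under recruitment and retention kept 526 of 598. The Introduction hypothesises that the effect persists at 2 weeks and that sound increases its magnitude and durability.

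**The concern.** Forced responses deal with skipped items inside a survey that someone opens. They do nothing about a T2 survey that is never opened, and that is the kind of missing data this trial will mainly have. The protocol answers it by leaving those people out at T2, although their baseline and T1 stigma scores are in hand and would inform the T2 estimate.

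The named method adds a second problem. A classical repeated-measures ANOVA needs a score at every time point in the model. If T1 and T2 go into one such model, T1-only participants also leave the T1 contrast, where the missing-data section says they belong.

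At stake are two stated hypotheses, persistence at 2 weeks and the durability benefit of sound. Both would rest on those who came back. With a target of only d=0.1, a modest selection effect is a visible share of what the trial is looking for.

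**Working it through.** **Inputs from the article.** 1500 per arm per country, so 4500 per arm pooled; d=0.1; one-sided alpha 0.01; attrition 20% (Sample Size); pilot retention 526/598 (recruitment and retention section). Dropout rates that differ by arm, and the stigma gap between dropouts and completers, are not in the article and are assumptions below.

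**1. The article's own figures.** 526/598 = 88.0%, so 12% were lost in the pilot. 1128/(1 − 0.20) = 1410: the attrition step reproduces. The 1128 itself does not follow from the stated inputs, since 2 × (2.326 + 0.842)²/0.1² gives 2008 per arm. That is a separate matter and nothing below uses 1128, but it explains why power at 1500 per arm comes out under 80%.

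**2. Participants without T2.** Per arm per country: 1500 × 0.12 = 180 to 1500 × 0.20 = 300. Per arm pooled: 540 to 900. Whole trial: 13,500 × 0.12 = 1620 to 13,500 × 0.20 = 2700.

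**3. T1, only if one classical T1-by-T2 ANOVA is fitted.** On simulated data with three time points and about 20% missing the last, a standard repeated-measures ANOVA routine refused the unbalanced data. Listwise deletion kept 243 of 300 subjects; a mixed model kept all 300. Power for an unadjusted two-arm comparison is Φ(d/√(2/n) − 2.326):

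| | All T1 completers | 12% lost | 20% lost |
|---|---|---|---|
| Per country, n per arm | 1500 | 1320 | 1200 |
| Power | 66.0% | 59.6% | 54.9% |
| Pooled, n per arm | 4500 | 3960 | 3600 |
| Power | 99.2% | 98.3% | 97.2% |

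**4. Bias at T2.** Let p be an arm's dropout rate and g its gap (mean of dropouts minus mean of completers, in SD). The completer mean lies p × g below the full-arm mean, so the arm contrast shifts by the between-arm difference in p × g.

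- Same p and same g in both arms: no shift, however strongly dropout depends on stigma.
- Assumed 20% vs 15%, g = 0.5: 0.05 × 0.5 = 0.025 SD, 25% of d=0.1.
- Assumed 12% vs 8%, g = 0.5: 0.04 × 0.5 = 0.020 SD, 20% of d.
- The same rates with g = 0.3: 0.015 and 0.012 SD.
- Equal dropout, different gaps: a shift of 0.1 SD needs gaps that differ by 0.1/0.20 = 0.50 SD at 20% loss, or 0.1/0.12 = 0.83 SD at 12%.

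For scale, the pooled standard error at 20% loss is √(2/3600) = 0.024 SD, so a shift of 0.025 SD is about one standard error. If the arm with more dropout is an intervention arm and its dropouts are the more stigmatising, the shift flatters the intervention.

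**The case against.** The strongest reply is that the article never says T1-only participants leave the T1 analysis. It speaks of ANOVAs in the plural, lists the T1 and T2 comparisons separately, and refers to an immediate effect analysis that keeps these people. With baseline collected, a baseline-to-T1 model and a baseline-to-T2 model are possible, and the first would lose nobody who completed T1. This stands: the T1 loss is conditional on how the ANOVA is built. But Primary Outcomes names only T1 and T2 as the measures compared, so the conflicting construction is left open, and T2 is completer-only under either.

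A reader might infer that the exclusion at the end of the missing-data section flatly contradicts the rule before it. The wording does not support that. Not answering at either time point can mean at neither, and the preceding sentence keeps T1-only participants explicitly. It is ambiguous and needs rewording.

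A reader might also infer that a completer analysis is unbiased only when dropout is unrelated to stigma. That is too strong: dropout related to stigma alike in all arms need not bias the contrast. Nor does the article make the arm main effect, averaged over T1 and T2, the test; it specifies a comparison at each time point.

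On size, the assumed gaps have no source in the article. A larger figure (0.037 and 0.025 SD) arises if the 0.5 SD is measured against the whole-arm mean, but the natural comparison is with completers, which gives the smaller values used here. Baseline adjustment would remove part of any gap already present at baseline. Finally, details such as covariance structure can be left to an analysis plan. The completer rule and the choice of ANOVA cannot be set aside that way, because this article fixes them.

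**Conclusion.** The concern holds in a bounded form. The article fixes a completer-only 2-week comparison while expecting 12% to 20% to miss T2, and its assurance about missing values covers items, not surveys. That follows directly from the text.

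Two further consequences are conditional. T1-only participants are lost from the T1 contrast only if T1 and T2 enter one classical repeated-measures ANOVA; the cost would then be up to 11 percentage points of per-country power and about 2 points pooled. The T2 contrast is biased only if dropout relates to stigma differently by arm; under the assumed scenarios with a 0.5 SD gap the shift is 0.020 to 0.025 SD, or 20–25% of d=0.1, and less with smaller gaps. The documents do not show that such bias will occur. The change is worth making because the scores that would reduce it are already being collected.

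**What to change.** 1. Make the primary analysis a likelihood-based longitudinal mixed model with baseline, T1 and T2 scores from all randomised participants who have any outcome data, with arm-by-time terms.
2. Take from it the arm contrasts at T1 (immediate effect) and at T2 (persistence), and the contrast of Intervention A minus Intervention B over time for the durability of sound.
3. Keep the completer comparison as a sensitivity analysis. Add one for dropout that is not missing at random, since the model corrects only for dropout explained by observed scores.
4. Reword the final exclusion sentence of the missing-data section so that it plainly does not remove T1-only participants. Do not simply delete it: it also carries the rule on people who did not watch the video, which is a separate question.
5. Limit the assurance about missing values to items within a completed survey.

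The cost is analysis wording and standard R code. No new data are needed, and the article reports that none had been collected as of March 2025.

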### Randomization, Consent, and Study Design

After reviewing the Institutional Review Board-approved information sheet, delivered to prospective participants online via ProA, those who indicate their consent to take part in the study will then be randomly assigned to one of three groups:

Intervention A: receiving the SAS video full intervention group.Intervention B: receiving the SAS video partial intervention (without sound) group.Control Group: receiving written information about addiction prevalence.

A baseline survey will be used to collect demographic information as well as baseline data on our primary and secondary outcomes. Thereafter, the Intervention A group will watch the 2.5-minute video, the Intervention B group will watch the 2.5-minute video without sound, and the control group will read a fact sheet about the global burden of addiction. Following this, all groups will complete a series of validated questionnaires to assess our primary outcome: addiction stigma, and secondary outcomes: optimism, warmth toward the subject, and hopefulness.

We will conduct the first round of surveys immediately post exposure of the intervention groups to the SAS video interventions and the control group to their written fact sheet. Follow-up assessments, using the same surveys, will be conducted 2 weeks later. To ensure the accuracy and validity of the results, we will include attention checks and exclude participants who fail these checks. Each participant will spend approximately 8 minutes watching the intervention and completing the surveys and will receive US $4.80 for completing the study. Figure 1 represents the trial design and flow.

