#### Recruitment and Strategies to Improve Adherence to Interventions, Promote Participant Retention, and Complete Follow-Up

Reaching adequate participant enrollment for our target sample size relies on our choice of ProA as a recruitment platform. ProA has a sufficiently large database of registered prospective trial participants in the United States, the United Kingdom, and South Africa. To improve survey completion rates in this trial, we offer payment to all participants. Participants will receive half of their payment after Step 1 of the study and the remaining half after completing Step 2 of the study. If participants spend more than 45 minutes on any phase of the trial, they will be timed out of the experiment. This prevents participants from bottlenecking the survey platform with partially completed questionnaires. We also conducted a pilot trial with 600 participants in the United States only to verify participant retention. In this pilot study, 88% (526/598) of participants returned to complete the follow-up surveys, underscoring the feasibility of this trial [32].

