#### Participant Timeline

Participants will be enrolled over a period of 4 weeks via the ProA platform. Step 1 of the trial (baseline data collection, video viewing, and T1 surveys) will occur on a rolling basis, with Phase 2 (follow-up surveys) taking place 2 weeks later across all arms. After both study phases have been completed, all participants will be offered posttrial access to the intervention video. Their voluntary view times will be recorded as a measure of participant engagement with this health education medium (Table 1).

**Table 1 table1:** Schedule of enrollment, interventions, and assessments.

Trial Information			Enrollment			Allocation			Close-out								
Time point			–t_1_			0			Intervention videos (t_1_)		Surveys (t_1_)		2-week interval		Surveys (t_2_)		Posttrial SAS^a^ video access

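### Non-viewers are excluded after randomisation by a rule that, in the Methods, can act only on the two SAS arms, and no as-randomised analysis is stated

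*Protocol article*

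**What the plan says.** **Order of events.** Under Randomization, Consent, and Study Design, "those who indicate their consent to take part in the study will then be randomly assigned to one of three groups". The baseline survey is described after that: "A baseline survey will be used to collect demographic information as well as baseline data on our primary and secondary outcomes". Participant Timeline groups baseline with exposure: "Step 1 of the trial (baseline data collection, video viewing, and T1 surveys) will occur on a rolling basis". Table 1 sets allocation at time 0, ahead of these steps.

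**Exclusions.** Four rules are stated:
- Viewing, in the section on nonadherence and missing data: "Participants who do not watch the videos or answer the questionnaire items at either time point will be excluded from the analysis".
- Attention, in the section on study design: "we will include attention checks and exclude participants who fail these checks".
- Completeness, in the section on discontinuing interventions: "Incomplete survey data will not be used in the primary analysis".
- Time limit, in the section on recruitment and retention: "If participants spend more than 45 minutes on any phase of the trial, they will be timed out of the experiment".

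For someone who completes T1 but not T2, the nonadherence section says that "their data will be included only in the immediate effect analysis". No analysis of all randomised participants is stated.

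**Control exposure.** The study-design section gives the control arm a written fact sheet. The hope-scale prompt under Attitude also refers to a fact sheet for controls, and the control row of Table 1 has one tick fewer than the intervention row. The Abstract instead gives the third arm an educational video.

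**The concern.** Randomisation makes the arms comparable only as long as the analysed groups are the randomised groups. A rule that removes people for what they did with their assigned exposure, and that exists for some arms only, breaks this. If people who skip a film about addiction hold more stigma than those who watch it, removing them from the video arms lowers mean stigma there even when the film does nothing, while their counterparts stay in the control arm.

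The trial targets a very small effect (d=0.1) with large arms, so a small selection effect can matter, and a larger sample does not cure it. The sound-versus-silent contrast, which is meant to isolate sound design, is exposed in the same way if the two versions are skipped at different rates or by different people.

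**Working it through.** **1. Which rules can differ by arm (on the Methods description)**

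| Rule | Whom it can remove | When it acts |
|---|---|---|
| Video not watched | SAS arms only | At exposure |
| Attention check failed | All arms | Not stated |
| Survey incomplete, or over 45 minutes | All arms | Any point after allocation |

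Only the first is asymmetric as written.

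**2. Who is removed needlessly.** The nonadherence section says that survey items must be answered before the participant can move on. Someone who skips the film and finishes the surveys therefore has complete outcomes and is still dropped. Someone who leaves at the film page has no T1 outcome and is lost under any rule. The bias specific to the viewing rule comes from the first group.

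**3. The plan's own figures.** The document gives no share of non-viewers and no stigma difference for them. Its only related allowance is 20% attrition: 1128 / 0.80 = 1410, which reproduces. Nothing below depends on the 1128.

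**4. Inputs**
- From Sample Size: d=0.1; one-tailed Type I error 0.01 (critical value 2.326); 1500 recruited per arm per country, so 3 × 1500 = 4500 per arm overall.
- Assumed: a share x of a video arm completes the surveys without watching, range 1% to 10%.
- Assumed: their mean stigma is g SD above that of the viewers, range 0.2 to 1.0 SD.
- Assumed: no control is excluded, the film has no effect, and scores are compared without baseline adjustment.

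**5. Formulae**
- Full-arm mean = viewers' mean + x·g, so dropping non-viewers from the video arm alone gives bias = x·g.
- SE = √(1/n + 1/(n(1−x))).
- False-positive rate = 1 − Φ(2.326 − x·g/SE).

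For x = 0.05, g = 0.5, n = 1500: bias = 0.025; SE = √(1/1500 + 1/1425) = 0.0370; 0.025/0.0370 = 0.676; 1 − Φ(1.650) = 0.049.

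| x | g (SD) | Bias (SD) | Share of d=0.1 | False-positive rate, 1500 per arm | 4500 per arm |
|---|---|---|---|---|---|
| 1% | 0.2 | 0.002 | 2% | 0.012 | 0.013 |
| 2% | 0.5 | 0.010 | 10% | 0.020 | 0.032 |
| 5% | 0.5 | 0.025 | 25% | 0.049 | 0.124 |
| 10% | 0.5 | 0.050 | 50% | 0.160 | 0.493 |
| 10% | 1.0 | 0.100 | 100% | 0.633 | 0.989 |

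After the planned 20% attrition (1200 and 3600 per arm), the 5%, 0.5 SD row gives 0.043 and 0.100.

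**6. Check by simulation** (5%, 0.5 SD, 1500 per arm, 4000 runs, no true effect):
- Exclusion in the video arm only: 0.050.
- The same kind of person dropped at the same rate in both arms: 0.011.
- Everyone kept as randomised: 0.010.

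The asymmetry drives the error.

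**7. Sound versus silent.** If the same kind of person skips each version, the bias is (difference in skip rates) × g. With 5% and 2% (assumed) and g = 0.5 it is 0.03 × 0.5 = 0.015 SD. With equal rates it is zero.

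**The case against.** **Attention checks.** A reader might infer that every exclusion in this plan destroys the randomised comparison. The documents do not support that. The attention rule applies to all arms. If the checks sit in the baseline survey, failure precedes any exposure and should not depend on arm; excluding on it then narrows the population without systematic bias, even though allocation has already happened. The checks are a threat only if they follow exposure or failure depends on arm, and their timing is not stated.

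**Control exposure.** If the Abstract's educational video were the true control, the viewing rule could cover all three arms and the asymmetry would shrink. The Methods, the hope prompt and Table 1 point to a fact sheet, but the conflict is real. Exclusion by viewing after randomisation would remain either way.

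**Reach of the rule.** The protocol does not say how non-viewing is detected or whether the film page can be skipped. The 3-second threshold under Methods for Additional Analyses concerns voluntary post-trial viewing only. If few people can skip the film and still finish, little is lost. This stands as a limit on size.

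**Direction.** Paid participants may skip to save time, unrelated to stigma. People with experience of addiction may skip and hold less stigma, which would bias against the film. It is tempting to read the table as showing that the trial will favour the video; it shows only what follows if g is positive.

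**Baseline adjustment.** If skippers differ because of stigma they already held, baseline stigma captures part of that, and all of it if skipping depends only on measured baseline. The primary-outcome section names T1 and T2 means, repeated-measures ANOVA, and regression on demographic and other variables as needed; it does not say that baseline stigma enters. The tabulated figures are therefore not established for the analysis that will be run.

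None of this supplies a reason to drop completers from their allocated arm.

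**Conclusion.** The point stands for the viewing rule. It acts after randomisation, it discards usable outcomes, and on the Methods description it can remove people from the SAS arms only. It can bias SAS versus control, and sound versus silent if skipping differs between versions.

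The size is unknown. Over the assumed ranges the bias runs from 0.002 SD, which is negligible, to 0.10 SD, which equals the whole design effect; 5% and 0.5 SD give 0.025 SD. These figures assume no baseline adjustment and no exclusion of controls. The sign follows from who skips, on which the document is silent. A definite inflated false-positive rate should not be read into it.

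Two related inconsistencies need reconciling: the control exposure (Abstract against Methods), and the phrase on either time point in the viewing rule, which sits awkwardly with keeping T1 completers who miss T2.

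The sponsor should fix this, but it does not invalidate the design.

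**What to change.** 1. Define the primary analysis, at each time point, as all randomised participants with outcome data at that time point, in their allocated arm, regardless of viewing.
2. Exclude only on attention checks placed before exposure, ideally before the randomiser, so that inattentive people are never allocated.
3. Keep the watched and attentive set as a sensitivity analysis, with an equivalent minimum-exposure rule for the fact-sheet page.
4. Report exclusions by arm and by reason, including people who leave at the exposure page.
5. Reconcile the Abstract's educational video with the fact sheet in the Methods, and reword the viewing rule so that it agrees with the handling of T2 non-completers.

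**Cost.** Changes to wording and the order of survey blocks. The article states that recruitment had not begun. If it since has, the blocks can no longer be reordered, but items 1, 4 and 5 remain possible provided non-viewers' responses are retained, and the sensitivity analysis in item 3 too if time on the fact-sheet page was logged. The statistical price is slight dilution: if 5% do not watch and gain nothing, d=0.1 becomes 0.95 × 0.1 = 0.095. That diluted effect is closer to the stated aim of evaluating the film as it would be met outside an experiment.
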